**8.2. Sample size**

The sample size has been calculated to demonstrate a clinically significant better completion with the 3HP or 4R regimens than the 3HR regimen. With an α= 0.025, β= 0.20, and 5% expected losses, and assuming a 0.75 proportion of treatment completion in the control arm (3HR), according to our previous experience, 225 subjects (75 per arm) will be needed to demonstrate, if exists, a 0.16 increase in treatment completion rates in the experimental arms (4R or 3HP) respectively. Sample size was calculated with GIGAcalculator (<https://www.gigacalculator.com/calculators/power-sample-size-calculator.php>).

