**3.2. Trial type**

Prospective, open-label, randomized (1:1:1), superiority, multicentre clinical trial with parallel group design, comparing three short-course rifamycin-based regimens for the treatment of latent TB infection in patients with end-stage kidney disease.

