**8. STATISTICAL METHODS**

**8.1. Statistical analysis**

The efficacy analysis will be performed on the modified intention-to-treat population, which will consist of all randomized subjects. The proportions of participants who completed the assigned treatment in the 3HR arm (control) will be compared with the proportions in either 3HP arm (experimental 1) or 4R arm (experimental 2). Since renal replacement therapy could have a potential influence on medication tolerance, especially INH, and thus could influence outcome, the analysis for the primary endpoint will be performed for the population as a whole and by subgroups (non-dialysis, on haemodialysis, or on peritoneal dialysis).

For safety, analyses will be performed on all randomized subjects who have received at least one dose of the assigned study treatment. Likewise, proportions of permanent discontinuation of the assigned treatment, related and unrelated to the study medication, and death, in the control arm will be compared with either experimental arm.

Statistical analyses will be performed by two investigators of the Biostatistics Unit of the IDIBELL, who will remain unaware of the trial-group assignments until the analyses have been completed. Differences between arms will be tested by Student’s t-test, if normally distributed, or a Wilcoxon two-sample test, if not normally distributed, or by chi-square analysis for categorical variables. Whenever possible, estimators will be given 95%CI. Statistical significance was set at a p-value <0.025. Treatment of the data and analysis will be performed with the statistical package R, version 3.4.1 or superior.

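### 75 per arm does not give the stated 80% power for each comparison of 0.75 with 0.91 at α = 0.025, whether α is one- or two-sided

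*Protocol*

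**What the plan says.** Protocol section 8.2 gives the whole calculation. The error rates and loss allowance are "With an α= 0.025, β= 0.20, and 5% expected losses". Completion on 3HR is taken as 0.75, from the investigators' own experience. The target is "a 0.16 increase in treatment completion rates in the experimental arms (4R or 3HP) respectively", that is, 0.91 in each experimental arm. The result is "225 subjects (75 per arm) will be needed to demonstrate, if exists, a 0.16 increase in treatment completion rates". An online calculator is cited as the tool.

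Section 8.1 describes the analysis. Each experimental arm is compared with control, the completion proportions are tested "by chi-square analysis for categorical variables", and "Statistical significance was set at a p-value <0.025". Efficacy is analysed in a "modified intention-to-treat population, which will consist of all randomized subjects". Section 3.2 describes the trial as "Prospective, open-label, randomized (1:1:1), superiority, multicentre clinical trial with parallel group design". Neither 8.1 nor 8.2 says whether 0.025 is one- or two-sided.

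**The concern.** Section 8.2 is the only justification for the enrolment target, and it states every input needed to check the result except the sidedness of α. At these rates 75 per arm looks too small for 80% power at an α as strict as 0.025.

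If so, a null result for 3HP or 4R would be read as coming from a comparison with a one-in-five chance of missing the planned effect, when the real chance is larger.

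The 5% allowance raises a second question. Inflating for losses presumes that lost participants leave the analysis, but section 8.1 keeps all randomised subjects in it.

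**Working it through.** **Inputs (section 8.2).** Control p₀ = 0.75; experimental p₁ = 0.75 + 0.16 = 0.91; mean 0.83; α = 0.025; power 0.80 (z = 0.8416); losses 5%; 75 per arm, so 75 × 0.95 ≈ 71 evaluable. Because sidedness is not stated, both readings are shown.

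**Step 1: try to reproduce 75.** The pooled two-proportion formula is

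n = [z_α √(2 × 0.83 × 0.17) + 0.8416 √(0.75 × 0.25 + 0.91 × 0.09)]² / 0.16²

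The two square roots are 0.5312 and 0.5190, so the second term is 0.4368.

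- Two-sided 0.025 (z = 2.2414): (1.1907 + 0.4368)² / 0.0256 = 103.5, so 104 evaluable. 104 / 0.95 = 109.5, so 110 randomised per arm (330 in total).
- One-sided 0.025 (z = 1.9600): (1.0412 + 0.4368)² / 0.0256 = 85.3, so 86 evaluable. 86 / 0.95 = 90.5, so 91 randomised per arm (273 in total).

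Other formulas without continuity correction (unpooled, arcsine, fully pooled) give 100–105 evaluable two-sided and 82–87 one-sided. A continuity correction raises the need to 116 and 98. None gives 75, or 71 before losses.

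The nearest match for a single comparison changes the stated α to one-sided 0.05: 65–69 evaluable, or 69–73 with losses, depending on the formula.

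**Step 2: power with the planned number.** From the same formula, power = Φ[(0.16√n − z_α × 0.5312) / 0.5190]. For example, n = 75 two-sided gives (1.3856 − 1.1907) / 0.5190 = 0.376, so 64.6%. The exact column enumerates the two binomials for the uncorrected chi-square test.

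| α = 0.025 | n per arm | Formula | Exact |
|---|---|---|---|
| two-sided | 75 | 64.6% | 65.6% |
| two-sided | 71 | 61.9% | 62.3% |
| one-sided | 75 | 74.7% | 76.5% |
| one-sided | 71 | 72.3% | 73.9% |

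**Step 3: difference detectable with 80% power from 0.75** (same formula). Two-sided: 0.183 at n = 75 and 0.187 at n = 71. One-sided: 0.169 and 0.173.

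**Step 4: power to win at least one of the two comparisons.** Simulation with a shared control arm, both experimental arms truly at 0.91, 400,000 replicates. Two-sided: 80.3% at n = 75 and 77.7% at n = 71. One-sided: 88.5% and 86.6%.

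**Step 5: losses.** Suppose that the 5% lost stay in the denominator as non-completers, and that 0.75 and 0.91 refer to participants who are not lost. The rates become 0.95 × 0.75 = 0.7125 and 0.95 × 0.91 = 0.8645, a difference of 0.152. Exact power with n = 75 is then about 52% two-sided or 64% one-sided.

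**The case against.** The best defence is that the trial was sized to win at least one comparison. The primary objective in section 2 asks whether either regimen, or both, is better than 3HR. On that reading 75 per arm gives about 80% two-sided before losses, and 87–88% one-sided even after them. This is a reasonable aim, and if it was intended the number may be adequate. But section 8.2 attaches the 0.16 increase to 4R and 3HP respectively, which is a claim about each comparison. The match is also inexact: two-sided power drops to 78% once the stated losses are applied, and one-sided power is well above 80%.

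A second defence is that the hypothesis is directional, so one-sided 0.025 may be meant. That is possible, although a chi-square test is ordinarily two-sided. It narrows the shortfall to about 4–6 points (exact) but does not remove it.

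Three stronger readings are tempting, and the document does not support them:

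- A reader might infer that the trial misses the planned effect one time in three. That holds only if α is two-sided; one-sided it is about one in four.
- A reader might take 52% or 64% as the real power. Those figures assume that 0.75 and 0.91 exclude losses. If the earlier experience behind 0.75 already counted losses as non-completion, the dilution would be counted twice. The protocol does not say which, and states no rule for lost participants.
- A reader might conclude that one-sided 0.05 was entered in the calculator. The number is close to that, but nothing in the text shows it.

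**Conclusion.** The sample size statement is wrong as written. Under either sidedness of the stated α, 75 per arm does not give 80% power for each comparison of 0.75 with 0.91.

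Per-comparison power is 62–66% two-sided, a miss rate of about one in three, or 74–77% one-sided, about one in four. These figures rest on the uncorrected chi-square test and 71–75 evaluable per arm. They do not depend on how losses are counted in the analysis; that question could lower power further, but only under the assumption given in the working.

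The finding concerns the power claimed for 75 per arm. It does not show that the trial must enrol more.

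**What to change.** Revise section 8.2, without changing enrolment:

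1. State whether α = 0.025 is one- or two-sided, and use the same wording for the threshold in section 8.1.
2. State whether power is for each comparison or for winning at least one.
3. Restate the power or detectable difference for 75 per arm on that basis, with and without the 5% losses. Per comparison, the two-sided text would give about 66% (75 evaluable) and 62% (71 evaluable) for 0.75 against 0.91, with 0.18–0.19 detectable at 80% power. The one-sided text would give about 77% and 74%, with 0.17 detectable. If at least one win is meant, say so and give 80% and 78% two-sided, or 88% and 87% one-sided, on the assumption that both experimental arms are truly at 0.91.
4. Reconcile the 5% allowance with the analysis of all randomised subjects: say how a lost participant is counted, and whether 0.75 and 0.91 already include losses. If losses count as non-completion and are not already in those rates, give power on the diluted rates instead of inflating the sample.

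The cost is an amendment to the protocol wording and, on any per-comparison reading, a less favourable stated power.

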**9. ETHICS**

The Investigator will ensure that this study is conducted in accordance with the principles of the Declaration of Helsinki, ICH Guidelines for Good Clinical Practice and RD 1090/2015), and in full conformity with relevant regulations

The protocol, informed consent form (ICF), participant information sheet (PIS) and any applicable documents will be submitted to an appropriate Ethics Committee (EC) and Regulatory Authority (AEMPS) for written approval. All substantial amendments to the original approved documents will be also sent to an appropriate Ethics Committee (EC) and Regulatory Authority (AEMPS) for written approval.

**9.1. Informed consent**

The participant must personally sign and date the latest approved version of the informed consent form before any study-specific procedures are performed.

Written and verbal versions of the Participant Information Sheet (PIS) and Informed Consent Form (ICF) will be presented to the participants detailing no less than: the exact nature of the study; the implications and constraints of the protocol; the known side effects and any risks involved in taking part. It will be clearly stated that the participant is free to withdraw from the study at any time for any reason without prejudice to future care, and with no obligation to give the reason for withdrawal.

The participant will be allowed as much time as wished to consider the information, and the opportunity to question the Investigator or other independent parties to decide whether they will participate in the study. Written Informed Consent will then be obtained by means of participant dated signature and dated signature of the person who presented and obtained the informed consent. The person who obtained the consent must be suitably qualified and experienced and have been authorized to do so by the Principal Investigator. For its obtention, the responsible investigators will comply with the current legislation (RD 1090/2015) and ethical principles of the Helsinki declaration. A copy of the signed ICF will be given to the participants. The original signed form will be retained at the study site *(attachment 3)*.

**9.2. Subjects’ confidentiality**

Treatment, communication, and cession of personal data of all the participants in the study will be guided by the Organic Law 3/2018 of 5 December on the Protection of Personal Data and Guarantee of Digital Rights (LOPDPGDD)." Data collected for the study will be identified by a code, and only the authorized investigators will be able to relate the participant's data with their names and clinical identification code.

**10. FUNDING AND INSURANCE**

- **Funding.** The trial is funded with a grant of 149,435€ through a competitive call, by the Instituto de Salud Carlos III of the Ministry of Science and Innovation of the Spanish Government, (Acciones Estratégicas de Salud 2021. Grant number: PI21/004444).
- **Insurance.** Insurance will be contracted to cover the civil liability that may arise from the sponsor and the investigator for the damages caused to the participants. The available budget for the insurance is 15,000€.

**11. AGREEMENT TO PUBLISH**

[name] [name], as Sponsor of the trial, agrees to make publicly available the main study results, regardless of their outcome.

**12. ATTACHMENTS**

**Attachment 1a.** Data sheet of Cemidon®

**Attachment 1b.** Data sheet of Rifaldin®

**Attachment 1c.** Data sheet of Rimactán®

**Attachment 1c.** Data sheet of Priftin®

**Attachment 2.** Scheduled assessment visits

**Attachment 3a.** Informed consent form

**Attachment 3b.** Appendix
